# A comparative study on the clinical effect of the treatment of pathological scars in young and middle-aged women with the combination of Chinese and western medicine

**DOI:** 10.1097/MD.0000000000020623

**Published:** 2020-06-19

**Keywords:** clinical trials, pathological scars, traditional Chinese medicine

## Abstract

**Introduction::**

Pathological scar is the abnormal manifestation of skin fiber hyperplasia caused by the failure of normal healing after skin damage. At present, there are many clinical treatments for pathological scars. However, there is no cure for clinically effective pathological scars with high recurrence rate. In this study, we will use a combination of Chinese and western medicine treatment methods to evaluate the clinical efficacy and related indicators of young and middle-aged female patients who meet pathological scars, looking for an objective and effective treatment method for pathological scars.

**Methods/design::**

In this study, we will use our own front-to-back clinical research method. We plan to include 120 young and middle-aged female patients who meet the diagnostic criteria for pathological scars. The untreated pathological scars of the enrolled patients will be used as blank controls. The intervention group will be given conventional western medicine treatment and combined Chinese and western medicine treatment. The assessment of scar area, color, hardness, thickness, itching, and pain was recorded for 8 weeks of treatment.

**Discussion::**

This trial may provide evidence regarding the clinical effectiveness, safety, and cost-effectiveness of traditional Chinese medicine for patients with pathological scars.

**Trial registration::**

ClinicalTrials.gov, ChiCTR2000032187, Registered on April 22, 2020.

## Introduction

1

Pathological scars are the abnormal manifestation of skin fiber hyperplasia caused by the failure of normal healing after skin damage.^[1]^ At present, there are many clinical treatments for pathological scars. Clinically, it is mostly treated by surgery, hormone therapy, radiotherapy, and laser, but there is no cure for clinically effective pathological scars with high recurrence rate.^[2]^ Traditional Chinese medicine (TCM) has a unique understanding of pathological scars. TCM holds that the pathological scars is due to the deficiency of positive Qi after skin trauma, and the evil poison is stagnant on the surface of the skin, which gradually causes the phlegm and congestion of the body to form on the surface, thereby forming pathological scars. And it is related to their own constitution.^[3,4]^ Some Chinese medical experts hold that this is related to long-term dampness in the body or dampness of the lungs and stomach, coupled with skin trauma, stagnation of blood and blood stasis, and eventually pathological scars are formed. Therefore, in the treatment of pathological scars, TCM usually starts with the methods of promoting blood circulation and removing blood stasis, orally combined with external treatment, or supplemented with acupuncture and point injection. TCM has a good clinical effect on the treatment of this disease. At present, the pathogenesis of pathological scars is still unclear, but the theories supported by more scholars include genetics, vascular endothelial dysfunction, inflammation, and immunology.^[5]^ Pathological scars is mainly characterized by excessive inflammation. Modern medicine believes that pathological scars are related to the body's immune response.^[6,7]^ On the one hand, the inflammatory response stimulates the immune response, and the cytokines produced increase the inflammatory response. In contrast, the immune response also affects the inflammatory response. TCM plays a regulatory role in the body's systemic or local inflammatory and immune responses.

TCM is currently effective in preventing and treating pathological scars and has unique advantages. Oral administration of TCM, external application of TCM, acupuncture and moxibustion, and combination of traditional Chinese and western medicine can be selected. Through the analysis of syndrome differentiation of TCM, according to the actual situation of the patient, choose the appropriate prescription medicine to improve the patient's Qi stagnation, blood stasis and meridian obstruction pathogenesis as a whole, and then achieve satisfactory results. The mechanism of TCM treatment of pathological scars is mainly to inhibit the proliferation of fibroblasts and the synthesis of collagen. At present, we should fully integrate Chinese medicine pharmacology. Strengthen the research on the treatment of pathological scars with TCM, and screen out the drugs with the exact curative effect and less side effects to inhibit the scar hyperplasia. While giving full play to the advantages of TCM treatment, we should also draw on the advantages of Western medicine treatment and carry out integrated Chinese and western medicine treatment to improve clinical efficacy and reduce the recurrence rate. Although the curative effect of TCM on pathological scars is certain, there is a problem that the standard of curative effect is not uniform. Through the consensus of the Chinese medicine industry, the release of industry guidelines for the treatment of pathological scars by Chinese medicine, and the uniform evaluation of efficacy standards, are of great significance for the study of Chinese medicine treatment of pathological scars. Therefore, in this study, we will use our own front-to-back clinical research methods to evaluate the clinical efficacy and related indicators of young and middle-aged female patients who meet pathological scars, and to find an objective and effective treatment method for pathological scars.

## Methods/design

2

### Study design and settings

2.1

This study will be conducted at the Second Affiliated Hospital of Shaanxi University of Chinese Medicine. This protocol was written and based on Standard Protocol Items: Recommendations for Interventional Trials guidelines the participants will be informed about the research, procedures, risks, and benefits by [name] (author of this protocol). If they agree, they will sign an informed consent form. Only those participants who read and agree to the protocol and who sign the informed consent form will take part of the study, following the schedule described in Figure 1.

**Figure 1 F1:**
[figure not shown]
Study design flow chart.

### Participants

2.2

The subjects of this study will be included in the outpatient and hospitalized patients from the Department of Plastic Surgery of the Second Affiliated Hospital of Shaanxi University of Chinese Medicine, and meet the diagnostic criteria for pathological scars. The research subjects gave informed notification and signed the “*Informed Consent for Pathological Scars Clinical Research*.”

#### Diagnostic criteria

2.2.1

We will refer to the diagnostic criteria for pathological scars in “*Plastic Surgery*.”

1.Hypertrophic scars: scars caused by burns or trauma, surgery, grow like tumors, bulge on the skin surface, local thickening and hardening, not exceeding the original wound limit, the surface is reddish brown. Or accompanied by itching or pain is the main clinical manifestation.2.Keloids: bright red or auburn, swollen, hard-textured tumors caused by acne, chickenpox, injection, insect bites, piercings, etc caused by minor trauma or no obvious incentives, most of which develop from papules to nodules. The main clinical manifestation is continuous expansion in all directions, accompanied by strong pain and itching.

#### Inclusion criteria

2.2.2

This study will be conducted in China. Patients will be recruited from Plastic surgery departments of the Second Affiliated Hospital of Shaanxi University of Chinese Medicine. We will enroll participants based on the following inclusion criteria:

1.It meets the diagnostic criteria for pathological scars;2.There are at least 3 pathological healing scars throughout the body.3.Female patients of 16 ≤ age ≤ 40 years old;4.The time for the formation of fatigue marks exceeds 3 months;5.Those who have voluntarily signed the informed consent.

#### Exclusion criteria

2.2.3

Patients will be excluded if they meet the following criteria:

1.People with allergies and allergies to experimental drugs;2.Participants are between 16 and 40 years old;3.Patients with renal cancer, bladder tuberculosis, urinary stones;4.Patients with other malignant tumors;5.Patients with blood system diseases, coagulation dysfunction, and autoimmune diseases;6.Patients with severe cardiovascular disease, cerebrovascular disease, hematopoietic system disease, and neuropathy.

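### Exclusion criterion 2 removes ages 16 to 40, the same range that inclusion criterion 3 requires, so as written no patient is eligible

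*Protocol article*

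**What the plan says.** Section 2.2.2 (Inclusion criteria) opens with "We will enroll participants based on the following inclusion criteria". Its third item sets sex and age: "Female patients of 16 ≤ age ≤ 40 years old". The inequality signs make both end points part of the admitted range.

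Section 2.2.3 (Exclusion criteria) opens with "Patients will be excluded if they meet the following criteria". Its second item reads "Participants are between 16 and 40 years old". The item is a complete sentence in an intact numbered list. It contains no negation and no word that would turn it into a statement about ages outside the range.

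The abstract (Methods/design) gives the intended population and its size: "We plan to include 120 young and middle-aged female patients who meet the diagnostic criteria for pathological scars".

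**The concern.** An exclusion list should remove some of the patients whom the inclusion list admits. Here one exclusion item takes back the whole age range that the inclusion list requires. A patient who satisfies inclusion criterion 3 thereby meets exclusion criterion 2, and a patient who escapes exclusion criterion 2 fails inclusion criterion 3.

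Eligibility criteria define the population to which the results apply, and screening staff, monitors and the ethics committee work from them. Applied literally, these admit nobody. If site staff ignore the exclusion item and follow the inclusion item, every woman enrolled between 17 and 39 meets a written exclusion criterion under either reading of the end points. Each such enrolment would then be open to being recorded as an eligibility deviation. Any later analysis restricted to patients who met the eligibility criteria would lose them all.

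**Working it through.** No figure in the plan needs reproducing, because the question is one of set logic.

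**Inputs**

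| Input | Value | Source |
|---|---|---|
| Age required for entry | 16 to 40, both ends included | Section 2.2.2, item 3 |
| Age that triggers exclusion | 16 to 40, end points not specified | Section 2.2.3, item 2 |
| Planned enrolment | 120 women | Abstract, Methods/design |

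**Rule.** Eligible ages = ages admitted by the inclusion criterion, minus ages removed by the exclusion criterion.

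The number of whole-year ages admitted is 40 − 16 + 1 = 25.

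**Reading A: the exclusion range includes its end points.** This matches the notation of the inclusion criterion.

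- Ages removed: 16 to 40, which is 25 ages.
- Ages left: 25 − 25 = 0.
- Patients eligible out of the 120 planned: 0.

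**Reading B: the exclusion range leaves out its end points.**

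- Ages removed: 17 to 39, which is 39 − 17 + 1 = 23 ages.
- Ages left: 25 − 23 = 2, namely 16 and 40.

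Reading B does not rescue the criterion. It would confine the trial to the two extremes of the intended range.

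**Could all the exclusion items be required together?** The lead-in to section 2.2.3 does not say that any single item is enough. But if a patient had to meet every item at once, she would be excluded only if she had allergy to the study drugs, the listed renal and urinary conditions, another malignancy, blood and autoimmune disease, and severe cardiovascular and neurological disease simultaneously. Such a list would screen out practically nobody. The list works only if one item is sufficient, which is the usual convention.

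**Is the conflict resolved elsewhere?** The abstract, introduction and discussion describe the target group as young and middle-aged women. That agrees with the inclusion criterion and gives no support to the exclusion item. No section restates the exclusion in a corrected form. Both sections are current text, and nothing around either item is blacked out or missing.

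**The case against.** The strongest reply is that the intention is plain. The inclusion criterion gives the range with explicit inequality signs, the article repeatedly describes the population as young and middle-aged women, and the abstract plans to enrol 120 of them. Nothing suggests that anyone meant to exclude this group. The article has other wording slips, for example in the names it uses for scars in the inclusion criteria and outcome sections. A dropped negation is therefore the natural explanation, and site staff would hardly apply the item literally. The slip also leaves the endpoint, the power, the type I error and the randomisation untouched. It is better called an internal inconsistency than a design decision.

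Most of this is right, and it limits what can be claimed. An empty trial is the literal consequence of the text, not a realistic forecast. The article defines no per-protocol set or any other analysis set, so the effect on such a set is conditional on one being defined by eligibility. The registry record is not at hand, so it cannot be said to carry the same error.

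The reply explains how the error probably arose but does not remove it. The dropped negation is an inference that the document itself does not confirm. An eligibility criterion is an operative rule, and staff should not have to decide which of two written criteria to disregard.

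**Conclusion.** The concern holds. Inclusion criterion 3 and exclusion criterion 2 contradict each other, and nothing in the article reconciles them. Read literally, 0 of the 120 planned patients are eligible. On the narrower reading of the exclusion range, only women aged exactly 16 or exactly 40 are, which is 2 of 25 whole-year ages.

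The conclusion rests on one assumption: that meeting a single exclusion item is enough to exclude a patient. That is conventional and is the only reading under which the list has a function. The conclusion does not depend on how analysis sets are defined or on what the registry says.

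The error must be corrected before the first patient is screened, because it concerns the rule that defines the study population. It does not by itself show that the intended population is unsuitable.

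**What to change.** Make one of two changes in section 2.2.3:

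- Delete exclusion criterion 2. This is the cleaner choice, because inclusion criterion 3 already fixes the age range and the exclusion item adds nothing to it.
- Or reword it so that it excludes women younger than 16 or older than 40.

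Both changes give the same eligible ages, 16 to 40 inclusive, and restore the population that section 2.2.2 already states. Neither introduces a new rule. The sponsor should confirm that this is the intended range, then check the full protocol, the screening form and the registry entry, and correct any that carry the same wording.

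The cost is one line of text. Section 2.9 (Ethics) says that recruitment had not started and that the plan was still to go to the ethics committee, so the correction can be made in the version submitted. No sample-size or analysis work follows from it. If patients have been enrolled in the meantime, a formal amendment is needed, with a note for those already entered explaining that they were enrolled against the written exclusion item.

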#### Conditions for participants to suspend and withdraw from the clinical trial

2.2.4

Researchers participating in clinical trials should carefully record the reasons for the suspension of the trial and the relationship with the clinical trial. It is necessary to clearly record the unwillingness of the subjects to continue the clinical trials, put forward the reasons for withdrawing from the clinical trials, and record the evaluation indicators at the time of discontinuation in detail.

1.Those who cannot adhere to treatment;2.Allergic reactions or serious adverse reactions during the test, the test should be suspended:3.Those who have not been treated strictly according to the plan;4.People who withdrew from the study on their own

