### Interventions

2.3

The participants included in the observation will be self-controlled, and each patient randomly selected 3 different scar treatment areas at the same site as observation specimens.

Control group: Take the untreated pathological scars of the participants as blank control. This group will not give any intervention.

Intervention group: Among the two pathological scars, group A will be treated with conventional external medicine of western medicine, and group B will be treated with oral TCM decoction combined with conventional external medicine of western medicine. The main components of the TCM prescription are: *Baizhi, Jiazhu, Leiwan, Maidong, Yuanhu, Taoren, Honghua*, and *Jingjie*. Specific treatment method: clean the scar area, apply gel to the affected area, every 3 times. TCM decoction is taken orally after meals, 3 times a day. The total application time will be 8 weeks. At the same time, closely monitor the change of the condition in order to control the deterioration of the condition in time (Fig. 2).

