### Randomization and blinding

2.6

Participants will be randomly allocated to the 2 groups through a sequence of numbers generated by a computer program before starting the selection process. The group assigned to each patient will be kept in a sealed envelope with the objective of concealing the assignment to the researcher, who will decide on the entry of subjects to the study. Given the nature of the interventions, the physiotherapists, and the patients, blinding will not be possible. However, the evaluator and statistician will be blinded to which group the subjects evaluated will belong.

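### Section 2.2.4 makes non-adherence and departure from the plan grounds for leaving the trial, so week-8 outcomes may be missing selectively; the size and direction of any bias are unknown

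*Protocol article*

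**What the plan says.** The heading of section 2.2.4 is "Conditions for participants to suspend and withdraw from the clinical trial", so its list concerns leaving the trial and not only stopping treatment. Item 1 is "Those who cannot adhere to treatment" and item 3 is "Those who have not been treated strictly according to the plan". Item 2 concerns allergic and serious adverse reactions. Item 4 covers patients who leave of their own accord, so items 1 and 3 apply even to a patient who has not chosen to leave. On data, the section asks staff to note the reasons and to "record the evaluation indicators at the time of discontinuation in detail". It mentions no assessment after that.

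Four other places bear on the point:

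- **Section 2.3 (Interventions), design:** "The participants included in the observation will be self-controlled", with three scar areas per patient.
- **Section 2.3, treatments:** "group B will be treated with oral TCM decoction combined with conventional external medicine of western medicine". The regimen is "TCM decoction is taken orally after meals, 3 times a day", for 8 weeks.
- **Section 2.4 (Outcome measures):** weekly scar assessment with photographs over the 8 weeks. The primary efficacy index in 2.4.1 is the change in total score from before to after treatment, divided by the score before.
- **Section 2.6 (Randomization and blinding):** "Participants will be randomly allocated to the 2 groups". Patients and treating staff are unblinded; the evaluator and the statistician are blinded.

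**The concern.** Stopping or departing from treatment is one event; leaving observation is another. Section 2.2.4 merges them. If items 1 and 3 are applied as written, a woman who misses treatment is withdrawn, and the last score the section asks for is the one on the day she stops. The efficacy index needs a score after treatment. Hers is either absent or replaced by an earlier value taken at a time that depends on adherence.

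Two features make this more than a formality. Item 3 sets no threshold for what counts as strict treatment, so a minor lapse could qualify. And the people best placed to judge a lapse know the treatment. At stake is whether the week-8 comparison describes everyone allocated or mainly those who kept to the regimen.

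This is a rule on data collection. An analysis plan can define who is analysed, but it cannot recover week-8 scores that were never taken.

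**Working it through.** **1. The plan's own allowance for loss (section 2.5).** Inputs: difference 11 points on the Constant–Murley questionnaire, alpha 0.05, power 95%, 49 per group, raised by 20% to 60. No SD is stated, so 49 cannot be confirmed, only solved backwards.

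- n = 2(z₀.₉₇₅ + z₀.₉₅)² SD² / 11². Setting n = 49 gives SD ≈ 15.1 (two-sided). Over a range of SDs, n is 22 at SD 10, 49 at SD 15 and 86 at SD 20.
- Allowance: 49 × 1.2 = 58.8, so 59; or 49 / 0.8 = 61.25, so 62. The stated 60 lies within 2 patients of both.
- If 20% of 60 are lost, 60 × 0.8 = 48 remain, and power at SD 15.1 is 94.6%.

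On its own terms the allowance protects power. It does nothing about who is lost. The question is selection, not size.

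**2. Parallel-group reading (section 2.6).** Let dA and dB be the shares withdrawn, and k the mean outcome of those retained minus that of those withdrawn, in SD units with higher meaning better, taken as equal in both groups. In each group, retained mean − full mean = d × k, so

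- bias in B − A = k(dB − dA)
- se = √(1/[60(1 − dB)] + 1/[60(1 − dA)])
- type I error = 1 − Φ(1.96 − bias/se) + Φ(−1.96 − bias/se), with no true effect.

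The withdrawal splits and k are assumptions; the documents give neither.

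| dB | dA | k | Bias (SD) | Type I error |
|---|---|---|---|---|
| 20% | 20% | any from −0.5 to 1.0 | 0 | 5.0% |
| 20% | 5% | 0.5 | +0.075 | 6.7% |
| 20% | 5% | 1.0 | +0.15 | 11.9% |
| 20% | 0% | 0.5 | +0.10 | 8.1% |
| 20% | 0% | 1.0 | +0.20 | 17.8% |
| 20% | 5% | −0.5 | −0.075 | 6.7% |
| 20% | 0% | −0.5 | −0.10 | 8.1% |

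Worked line: 0.5 × (0.20 − 0.05) = 0.075; se = √(1/48 + 1/57) = 0.196.

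Bias needs both unequal withdrawal and an outcome gap. The sign of the gap sets the direction.

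**3. Self-controlled reading (section 2.3).** All conditions sit on the same woman, so withdrawing her removes all her scars at once. Any burden from the decoction is hers as a whole and cannot cause unequal loss between conditions. This was simulated with 2,000,000 patients:

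- prognosis u ~ N(0,1), shared by her scars; probability of adhering 1/(1 + exp[−(1.5 + u)])
- scar A = u + error; scar B = u + h·u + error; each error N(0,1)
- no average effect among all patients; about 22% withdrawn.

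With h = 0 (adherence related only to shared prognosis), the B − A difference among those retained is 0.00. With h = 0.5 (adherers also respond better to the combination), it is +0.09 in units of the between-patient SD. The SD of a single A scar in this model is √2 = 1.41, so that is 0.094 / 1.41 ≈ 0.07 of it. The values of h and the adherence model are assumptions.

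**The case against.** The strongest reply is that the text is being read too hard. Section 2.2.4 asks for indicators at discontinuation but does not forbid later ones. Section 2.4 schedules weekly assessment, the schedule figure is not shown, and no sentence says that withdrawn patients leave the analysis. The analysis population is commonly set in an analysis plan or full protocol, and neither is shown. Much of this stands: the silence on analysis sets is not a fault of this article, and it cannot be said that week-8 scores will certainly be missing. What the reply does not remove is the stated rule. Items 1 and 3 end trial participation, separately from voluntary withdrawal, and no follow-up is attached to them.

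A reader might go further and infer that withdrawals will come mostly from the oral regimen, and that the result will therefore flatter the combined treatment. The documents do not support this. No adherence figures by regimen are given, and the gel also has to be applied repeatedly. If those who stop are doing better than those who stay, the bias runs against the combination. Under the self-controlled design there is no unequal loss at all.

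Nor can the 20% allowance be turned into a bias in scar-score points. Section 2.5 applies it to both groups, and equal loss with an equal gap gives zero. Placing all of it on group B, and choosing a gap and an SD for the scar score, would be assumptions without a source.

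**Conclusion.** The defect holds in a narrow form under either design. Section 2.2.4 makes continued participation depend on adherence after allocation and states no assessment beyond discontinuation, so week-8 outcomes may be missing selectively and the result would then describe mainly adherent patients.

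Size and direction are unknown. Under parallel groups, bias arises if withdrawal differs between groups and those withdrawn have different outcomes. That only group B takes the decoction is one plausible route, not an established one. Under the self-controlled design, bias arises only if adherers respond differently to the combination. The figures above show how such bias would behave; they do not estimate it for this trial. The conclusion rests on reading the section's heading and items 1 and 3 literally. The wording should be changed before recruitment, which section 2.9 says has not begun, because outcomes not collected cannot be restored later.

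**What to change.** - **Section 2.2.4, items 1 and 3:** reword so that non-adherence and departure from the plan are recorded, with date and reason, but do not end trial participation. Reserve withdrawal from follow-up for patients who withdraw consent to it.
- **Follow-up:** state that the weekly scoring and photographs of section 2.4 continue to week 8 for these patients.
- **Analysis:** unless the analysis plan already says so, analyse all randomised units as allocated, with the strictly treated set as a sensitivity analysis. The unit is the patient or the scar, once sections 2.3 and 2.6 are reconciled.
- **Unchanged:** the rule on allergic and serious adverse reactions (item 2). Nothing here concerns when treatment itself should stop.

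The cost is a few lines of protocol text and some extra effort to keep already scheduled visits for patients who stop treatment.
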